#### Secondary outcomes

All secondary outcomes are hypothesis-generating. GOSE as an ordinal variable will be compared between treatment arms using a proportional odds model if the proportional odds assumption is justified [30, 31]. If not, a partial proportional odds model will be used [32, 33].

Binary variables (including hospital and six-month mortality and AEs) will be analysed with log-binomial [34] and identity-binomial regression models [35] to estimate risk ratios and risk differences with 95% CIs, respectively.

QOL measures and other continuous variables will be analysed with linear regression, using robust standard errors to accommodate potential non-normality and unequal error variation.

Analyses of time-to-event outcomes will use Kaplan–Meier plots and log-rank tests, as well as unadjusted and adjusted Cox proportional hazard regression models returning hazard ratios with 95% CIs.

QOL outcomes will be reported as means (with standard deviations) of the physical and mental health scores of the SF-12 [28] and as the proportion of reported health problems for each domain of the EQ5D-3 L [27]. Differences in QOL between groups will be assessed using two-sample t tests or Wilcoxon rank-sum tests as appropriate [20] for the SF-12 component scores and Fisher’s exact or Chi-squared tests for the proportions in each domain of the EQ-5D-3 L.

#### Cost-effectiveness analyses

Cost-effectiveness from the healthcare-payer perspective will be calculated as a cost per additional patient with a favourable neurological outcome at six months following randomisation (defined as GOSE 5–8) and the cost per additional quality-adjusted life year (QALY), with QALYs calculated using utility scores derived from the EQ-5D-3 L conducted at six months post randomisation. Costs will be determined based on resource use during the intensive care, acute and post-acute periods up to six months post randomisation. These will be valued using the UK time-trade-off tariff. All patients will be assumed to have a utility score of zero at randomisation in accordance with other studies recruiting patients in critical care. Patients who die before the six-month follow-up will be given a utility of zero.

Data on resource use at different levels of care will be recorded at discharge from the index hospitalisation and again at follow-up for subsequent healthcare resource use (including readmissions, rehabilitation and other care facilities). Information will be collected for length of ventilation, time in ICU, hospital (ward) days, rehabilitation days and time spent in high- and low-level care facilities and transitional living centres.

Resources will be translated into costs by multiplying the relevant country-specific unit cost by use for each patient in the analysis, where unit costs are obtained from hospital staff where possible, or national databases. All costs will be reported in 2017 prices using national consumer price index statistics from relevant countries. Purchasing power parity (PPP) statistics from the Organisation for Economic Co-operation and Development (OECD) will be used to translate costs to a common currency (United States Dollars, $US). Given the relatively short time period, costs will not be discounted.

Analyses will adjust for fixed effects across three geographical regions (Australia/New Zealand (ANZ), Europe and the Middle East) to account for potential heterogeneity which may arise, for example, through regional variations in treatment patterns. The issue of transferability in multinational trials will be addressed by estimating costs and effects for the same three geographical regions. Region-specific estimates will be obtained by interacting the treatment variable with regional fixed effects.

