### Randomisation

Randomisation 1:1 between trial hypothermia and normothermia was performed by paramedics or physicians using sequentially numbered, opaque, sealed envelopes (as used in the RICH [23] and RSI trials [24]), printed at the Australian trial coordinating office before distribution to sites. Envelopes were used because at the time of trial design it was not feasible to develop a centrally controlled, real-time electronic randomisation system across international emergency departments and pre-hospital ambulances services. The computer-generated randomised treatment allocation schedule (using Stata version 11 *ralloc* module http://fmwww.bc.edu/repec/bocode/r/ralloc.ado) [25] was stratified by hospital group or pre-hospital paramedic ambulance service with a permuted block scheme. Hospital strata were defined for participating hospitals in nine groups, comprising three Australian states (Victoria, Queensland, Western Australia), two localities in New Zealand (Auckland, Waikato) and four other countries (France, Switzerland, Saudi Arabia, Qatar). Stratification of pre-hospital randomisation schedules was also specified within the four networks where such enrolment was possible (Queensland, Victoria, Western Australia, France) (Table 2).

**Table 2 Tab2:** The count of strata incorporated within the block-randomised 1:1 hypothermia / normothermia treatment allocation schedule

Pre-hospital	Stratum no.	Hospital region	Stratum no.
Yes^a^	1	Victoria^a^	5
Yes^a^	2	Western Australia^a^	6
Yes^a^	3	Queensland^a^	7
Yes^a^	4	France^a^	8
No		Switzerland	9
No		Saudi Arabia	10
No		Qatar	11
No		Auckland	12
No		Waikato	13

^a^Participating pre-hospital ambulance services and their relevant regional hospitals within each of these Australia states and France were each included as separate strata within the computerised generation of randomisation envelopes

Patients who fulfilled the inclusion criteria and had no exclusion criteria were randomised by opening the next available opaque envelope within the ambulance or hospital emergency room.

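### The cost analysis adjusts for three two-country regions, although unit costs and randomisation strata are country-specific, so intervals for incremental cost may be slightly too wide

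*SAP article*

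**What the plan says.** Cost-effectiveness analyses sets out the costing: "Resources will be translated into costs by multiplying the relevant country-specific unit cost by use for each patient in the analysis". Unit costs come from hospital staff where possible and otherwise from national databases. OECD PPP statistics "will be used to translate costs to a common currency (United States Dollars, $US".

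The adjustment follows: "Analyses will adjust for fixed effects across three geographical regions", namely Australia/New Zealand, Europe and the Middle East. The reason given is "to account for potential heterogeneity which may arise, for example, through regional variations in treatment patterns". For transferability, "Region-specific estimates will be obtained by interacting the treatment variable with regional fixed effects".

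The Randomisation section describes 1:1 permuted blocks within strata. There are nine hospital groups: Australia contributes three, one per state, New Zealand contributes two, and the remaining groups are "four other countries (France, Switzerland, Saudi Arabia, Qatar"), with one group each. Table 2 adds four pre-hospital strata (Victoria, Western Australia, Queensland, France), which makes 13. None of the 13 crosses a national border.

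Cost-effectiveness is listed under Secondary outcomes, all of which the SAP calls hypothesis-generating.

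**The concern.** Because use is multiplied by a country's own unit costs, mean cost can shift from country to country by construction. PPP conversion does not equalise health-care unit prices, and the SAP does not say whether the PPP series is economy-wide or specific to health care. Some price difference between Australia and New Zealand, France and Switzerland, or Saudi Arabia and Qatar may therefore remain. Three regional effects cannot absorb it.

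Blocking within country makes the arms nearly balanced on country, so between-country cost differences contribute almost nothing to the real sampling error of the treatment comparison. A model without country leaves those differences in the residual, and the standard error counts them. At stake is a somewhat conservative interval for incremental cost.

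**Working it through.** The SAP states no figure for cost precision, so there is none to reproduce.

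**Inputs from the SAP.** Country-specific unit costs, PPP conversion and three region effects (Cost-effectiveness analyses); 1:1 blocks in 13 strata nested in six countries (Randomisation, Table 2); 511 randomised.

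**Assumed inputs, none given in the SAP.** Within-country coefficient of variation (CV) of cost 0.7 to 1.3; ratio r of mean costs between the two countries of a region, after PPP, 1.1 to 3; share s of the dearer country 0.5 or 0.1.

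**Formula.** Take the cheaper country's mean cost as 1. Within a region:

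- between-country variance B = s(1 - s)(r - 1)²
- within-country variance W = CV² × [(1 - s) + s r²]
- interval width with region only, relative to country effects = √(1 + B/W)

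**Worked case, r = 2, s = 0.5.** B = 0.25 × 1 = 0.25. With CV 1.0, W = 0.5 + 0.5 × 4 = 2.5, so the ratio is √1.10 = 1.049. With CV 0.7, W = 0.49 × 2.5 = 1.225, so the ratio is √1.204 = 1.097.

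**Excess width, region only against country effects:**

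| Residual ratio r | CV 0.7, s = 0.5 | CV 1.0, s = 0.5 | CV 1.3, s = 0.5 | CV 1.0, s = 0.1 |
|---|---|---|---|---|
| 1.1 | 0.2% | 0.1% | 0.07% | 0.04% |
| 1.25 | 1.2% | 0.6% | 0.4% | 0.3% |
| 1.5 | 3.9% | 1.9% | 1.1% | 1.0% |
| 2 | 9.7% | 4.9% | 2.9% | 3.4% |
| 3 | 18.7% | 9.5% | 5.8% | 9.5% |

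**Simulation check.** Six countries in three regions (assumed sizes 300/50, 80/30 and 30/20, total 510), blocks of four within country, gamma costs with CV 1.0, no treatment effect, ordinary least squares, 4,000 trials per row:

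| r | Region: true SD / mean SE / coverage | Country: true SD / mean SE / coverage | Width ratio |
|---|---|---|---|
| 1.25 | 0.0928 / 0.0937 / 95.3% | 0.0929 / 0.0932 / 95.2% | 1.005 |
| 1.5 | 0.1000 / 0.1000 / 95.0% | 0.1000 / 0.0984 / 94.6% | 1.017 |
| 2 | 0.1121 / 0.1161 / 95.9% | 0.1119 / 0.1107 / 94.5% | 1.049 |
| 3 | 0.1403 / 0.1571 / 97.2% | 0.1397 / 0.1407 / 95.3% | 1.117 |

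A simulated SD carries a Monte Carlo error of about 1/√(2 × 4,000) = 1.1%. The comparison of SE with true SD therefore cannot resolve effects of 1-2%. The width ratio compares both models on the same data and is steadier; it agrees with the formula.

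The true SD is almost identical under the two models (0.1121 and 0.1119 at r = 2). Without blocking, at r = 2, the region-only model has a true SD of 0.1188, a mean SE of 0.1166 and 94.7% coverage. The conservatism therefore comes from blocking by country and then leaving country out.

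A second simulation, with lognormal costs, CV 0.7 and robust standard errors, gave reported SE over true SD of 1.01, 1.02, 1.09 and 1.18 at ratios 1.25, 1.5, 2 and 3. With country in the model, the mean SE was within 2% of the true SD at every ratio.

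**The case against.** The three regions are a stated, reasoned choice. They serve the transferability estimates and match the region covariate in the adjusted models, so the SAP is consistent with itself. All of that stands, but the stated example concerns treatment patterns, and the text does not address price differences between two countries of one region.

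The section on sensitivity analyses of the primary and secondary outcomes plans mixed models with the randomisation strata as a random effect. Those strata are nested in country and cost-effectiveness is a secondary outcome, so this could absorb the country differences. However, the section does not name costs, and a sensitivity analysis does not change the main interval.

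The strongest objection is size. The SAP gives no cost SD, country counts, price ratios or interval method, and a condensed article may leave the last to a fuller plan. With a residual ratio up to 1.5 the effect is at most about 4%. Widening of 10-19% needs a threefold difference left after PPP, which nothing in the document suggests. This stands and limits the point to a conditional one.

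Country effects are also an incomplete cure. Prices act multiplicatively, so additive effects leave differences between countries in spread and in incremental cost. Unit costs obtained from hospital staff may also vary within a country.

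**Conclusion.** The main cost analysis leaves out a design factor that is tied to cost by construction. If cost levels differ between countries within a region after PPP conversion, model-based or robust intervals for incremental cost will be somewhat conservative: about 1-4% too wide at residual ratios of 1.25 to 1.5, and 5-10% at a ratio of 2. This rests on an assumed CV of 0.7 to 1.0, equal-sized countries and an interval method that the SAP does not state. It is a minor point.

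Three stronger readings are tempting and are not supported:

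- **The intervals are definitely too wide.** The documents supply none of the inputs needed to say so.
- **The cost difference is biased, or chance imbalance between countries distorts it.** Blocking keeps that imbalance small. The estimate is unbiased under both models and its true SD is nearly the same.
- **Every cost-effectiveness result is affected to this degree.** The calculation covers incremental cost only. The cost-effectiveness ratios also carry uncertainty in favourable outcome and QALYs, which unit prices do not scale.

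**What to change.** In Cost-effectiveness analyses, replace the three regional main effects in the main cost analysis with six country fixed effects: Australia, New Zealand, France, Switzerland, Saudi Arabia and Qatar. Keep the three-level treatment-by-region interaction for the transferability estimates; country is nested in region, so the two fit together.

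The cost is one line of wording and 6 - 3 = 3 extra parameters in about 500 patients. Using the 13 randomisation strata instead is equally acceptable and adds 13 - 3 = 10. The same sentence could state how the interval for incremental cost will be computed, and whether the planned mixed model with randomisation strata also applies to costs.

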#### Pre-specified subgroup analyses

Two interactions of particular prior interest will be assessed. The primary and secondary outcomes will be evaluated according to: (1) the presence of surgically evacuated intracranial mass lesions (Marshall score V) [36]; and (2) the presence of any intracranial mass lesion whether or not surgically evacuated (Marshall V or VI).

#### Dose effect / Intensity of cooling

Intensity of cooling in intervention arm patients will be categorised according to the time after randomisation to first reach one of two core temperature thresholds, being the limit of mild hypothermia 35 °C [9] and also 34 °C as an indicator of more intense [6] cooling below 35 °C towards 33 °C. Cooling intensity categories are defined as never achieving hypothermia and tertiles of time in those reaching hypothermia. Primary and secondary outcomes of patients in these intensity categories will be compared across categories and to standard care patients.

Differential effects of cooling on the primary and secondary outcomes will be assessed according to: (1) Marshall computed tomography (CT) scan classification V; and (2) Marshall V or VI. These will be performed using appropriate covariate by treatment interaction terms in the relevant regression models.

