### Trial population and eligibility

A total of 511 severe TBI patients have been enrolled in Australia, New Zealand, France, Switzerland, Saudi Arabia and Qatar. This 511-patient full analysis set will not include the initial eight patients who were treated within a pre-trial run-in phase. Fourteen emergency departments and five pre-hospital agencies were involved. Patients may have been enrolled in the pre-hospital setting, if specifically trained and qualified staff are available, or by medical staff in the emergency department of participating hospitals. The inclusion and exclusion criteria are presented in Table 1. Eligible patients were randomised to receive prophylactic hypothermia (33 °C for 72 h) or TBI care that is standard (for that hospital) (Figs. 1 and 2).

**Table 1 Tab1:** Inclusion and exclusion criteria

Pre-hospital inclusion criteria	Emergency Department inclusion criteria
• Blunt trauma with clinical diagnosis of severe TBI and GCS < 9 • Estimated age ≥ 18 and < 60 years • The patient is intubated or intubation is imminent	• Blunt trauma with clinical diagnosis of severe TBI and GCS < 9 • Estimated age ≥ 18 and < 60 years • The patient is intubated or intubation is imminent
Pre-hospital exclusion criteria	Emergency Department exclusion criteria

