• Clinical diagnosis of drug or alcohol intoxication as predominant cause of coma • Randomisation unable to be performed within 3 h of estimated time of injury • Estimated transport time to study hospital > 2.5 h • Able to be intubated without drugs • Systolic BP < 90 mmHg • Heart rate > 120 bpm • Cardiac arrest at the scene or in transit • GCS = 3 + un-reactive pupils • Penetrating neck/torso injury • Known or obvious pregnancy • Receiving hospital is not a study site • Evidence of current anti-coagulant treatment Known to be carer dependent due to a pre-existing neurological condition	• Clinical diagnosis of drug or alcohol intoxication as predominant cause of coma • Randomisation unable to be performed within 3 h of estimated time of injury • Able to be intubated without drugs • Persistent systolic BP < 90 mmHg • GCS = 3 + un-reactive pupils • Cardiac arrest at the scene or in transit • Clinically significant bleeding likely to require haemostatic intervention, for example: ○ Bleeding into the chest, abdomen or retro-peritoneum likely to require surgery ± embolisation ○ Pelvic fracture likely to require surgery ± embolisation ○ More than two long bone fractures requiring operative fixation • Penetrating neck/torso injury • Positive urine or blood pregnancy test • Evidence of current anti-coagulant treatment • Known to be carer dependent due to a pre-existing neurological condition • In the treating clinician’s opinion, ‘cooling’ is not in the patient’s best interest

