#### Sensitivity analyses of the primary and secondary outcomes

Sensitivity analyses of the primary and secondary outcomes will be performed using regression models adjusting for pre-specified baseline covariates as well as any covariate exhibiting substantial imbalance between randomisation arms, as recommended [37]. Linear and generalised linear model diagnostics, outlier assessment and remedial measures will follow standard approaches [30, 38].

Proportionality in ordinal logistic regression models will be assessed [39]. Also, the proportional hazards assumption across treatment arms in time-to-event analyses will be evaluated using scaled Schoenfeld residuals [40] and visual assessment of log-log plots.

Baseline variables to be included as fixed effects when developing adjusted outcomes models comprise the following:Geographic region (Australia and New Zealand, Middle East, Europe – three level nominal categorical)Age (integer values centred on overall median age of trial patients)GCS (integer values with a possible range of 3–15)Pupil reactivity (ordinal, three levels)Hypoxia (binary)Hypotension (binary)Marshall CT brain scan classification (nominal categorical, six levels) [39]Core temperature closest to time of randomisation (continuous)

Generalised linear mixed regression models will be applied with the same fixed effects covariate set while also incorporating as a random effect the multiple randomisation strata comprising hospital and pre-hospital research groups. In the event the above regression models do not accommodate the number of pre-specified covariates, sensitivity analyses will be simplified to adjust at least for POLAR treatment and the baseline extended IMPACT TBI probability of 6 month unfavourable outcome.

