##### As-treated and per-protocol analyses

POLAR will repeat the primary and secondary trial outcomes in two pre-defined exploratory analysis sets: (1) the subset of compliant patients assigned to cooling compared to all patients assigned to the control (‘per-protocol’ analysis); and (2) according to the actual treatment received (‘as-treated’ analysis) [7].

The per-protocol analysis subset will comprise control and intervention patients who are demonstrated retrospectively to have suffered a severe TBI, thus excluding those with initially low GCS < 9 not due to severe head injury but rather associated with transient influences, such as alcohol or drug effects.

For analytic purposes, the differential ‘dose’ of early cooling received by each patient will be summarised as the area (degree × hours) under the protocol-defined cooling baseline value of 35 °C within 72 h of randomisation. Each individual’s AUC will be estimated by the linear trapezoidal method [41] applied to temperature data ignoring missing values. Early death or loss to follow-up within 72 h of randomisation will by definition reduce the observed dose of cooling received by such patients. The intensity of cooling will also be summarised categorically, in increments of 1 °C from ≥ 38 °C to ≤ 32 °C, as the proportion of individuals whose lowest core temperature during the trial intervention days was in each of these temperature bands. A binary definition of ‘compliance with cooling’ will constitute an AUC at least 72 degree × hours, this being at least half that theoretically achievable in the first 72 h. This definition will be used to identify the per-protocol and as-treated populations.

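### The time-to-threshold tertiles put cooling-arm patients who were already at or below 35 °C (or 34 °C) at randomisation into the fastest-cooled group

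*SAP article*

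**What the plan says.** In the section Dose effect / Intensity of cooling, intervention-arm patients are "categorised according to the time after randomisation to first reach one of two core temperature thresholds". The thresholds are 35 °C and 34 °C, the second taken as a marker of more intense cooling. The grouping rule is: "Cooling intensity categories are defined as never achieving hypothermia and tertiles of time in those reaching hypothermia". Primary and secondary outcomes in these groups "will be compared across categories and to standard care patients".

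Table 1, under Trial population and eligibility, lists the entry criteria for the pre-hospital and emergency department routes. The inclusion side begins with "Blunt trauma with clinical diagnosis of severe TBI and GCS < 9" and adds age and intubation. The exclusions cover, among others, blood pressure, heart rate (pre-hospital only), timing, pupils with GCS, and cardiac arrest. For the emergency department route they also cover "Clinically significant bleeding likely to require haemostatic intervention" and a clinician's judgement that cooling would not serve the patient. No item on either route is a temperature.

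Core temperature nearest to randomisation is recorded. It appears as a continuous covariate in the list under Sensitivity analyses of the primary and secondary outcomes, but plays no part in defining the intensity categories.

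**The concern.** The section heading and the word *intensity* present the categories as a measure of cooling delivered. A patient who enters at, say, 34.8 °C and is allocated to hypothermia meets the 35 °C criterion at once. Whether the time is scored as zero or as the time of the first reading after randomisation, it is the smallest value the records allow, and the patient ranks among the fastest cooled. Patients who had to be brought down from a normal temperature, for whom the time does measure speed of cooling, are pushed towards the slower tertiles.

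At stake is what a gradient across tertiles would mean. If outcome is related to entry temperature for reasons other than treatment, a difference between the fastest tertile and the others could reflect who was cold on entry rather than how fast cooling worked. It could mask an effect of rapid cooling or suggest one that is not there. This arises within the cooling arm, before any comparison with standard care.

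**Working it through.** The section gives no figure to reproduce. The check has two parts: whether the rule admits the problem, and how large it could be.

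**1. Does the rule admit it?**
- Can a patient at or below 35 °C be randomised? Reading every criterion in Table 1 for both routes finds no temperature limit. The nearest item is the clinician's judgement about cooling; it is discretionary, not tied to temperature, and listed only for the emergency department route.
- Does the category rule set such a patient apart? No. The only groups are never reaching the threshold and three tertiles of time among those who reach it.
- Where does the patient land? With the shortest time, hence in the fastest tertile.

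**2. How large could it be?**

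Inputs:
- Randomised: 511, allocated 1:1 (sections Sample size, power and interim analysis schedule, and Randomisation). Cooling arm: 511 / 2 ≈ 255.
- q, the share of the cooling arm at or below 35 °C at randomisation: not in the document; assumed 5%, 10%, 20%.
- u, the share of the cooling arm never reaching 35 °C: not in the document; taken as 0, then 10% to 30%.

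Formulae:
- Tertile size = 255 × (1 − u) / 3.
- Already-cold share of the fastest tertile = 255q / tertile size = 3q / (1 − u), capped at 100%.

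If all reach 35 °C (u = 0), each tertile holds 255 / 3 = 85:

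| q | Already cold (255q) | Share of fastest tertile |
|---|---|---|
| 5% | 12.75 (about 13) | 12.75 / 85 = 15% |
| 10% | 25.5 (about 26) | 25.5 / 85 = 30% |
| 20% | 51 | 51 / 85 = 60% |

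If 10% to 30% never reach 35 °C, the tertiles shrink to about 76 down to 60 patients and the shares rise:

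| q | u = 10% | u = 20% | u = 30% |
|---|---|---|---|
| 5% | 17% | 19% | 21% |
| 10% | 33% | 38% | 43% |
| 20% | 67% | 75% | 86% |

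The factor of three makes a small share matter, because every already-cold patient goes into one third of those reaching the threshold. If such patients are scored zero and exceed one third of those reaching it, the first tertile cut-point is itself zero and the tied patients cannot be divided into tertiles.

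At 34 °C the same formula applies, with q now the share at or below 34 °C. That share cannot exceed the share at or below 35 °C, and the patient at 34.8 °C no longer qualifies at entry. With the same number reaching the threshold, the effect is therefore smaller.

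**The case against.** The strongest reply is that the size is assumed. Nothing in the document shows how many patients were at or below 35 °C on entry, and adjusting for baseline temperature does not show that its values go that low. That stands: the percentages are a range, not an estimate.

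A second reply is that intensity here may mean temperature attained rather than cooling delivered, in which case a patient cold at entry really is hypothermic earliest. The rule is coherent on that reading. But the groups could then not be read as speed of cooling, and the heading invites that reading.

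Third, baseline temperature is a pre-specified covariate. It may lessen confounding where it is used, but the list belongs to the adjusted sensitivity models, the intensity comparison is not named there, and adjustment does not correct a patient's category.

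A reader might infer more than the document supports:
- *That cold patients had bled or had a worse prognosis.* This is not documented. The blood pressure exclusions on both routes, the pre-hospital heart rate exclusion and the emergency department bleeding exclusion narrow that group.
- *That these patients were never cooled.* They are in the intervention arm and may be cooled afterwards; the point is only that trial cooling did not bring them to the threshold.
- *That the area-under-the-curve dose needs the same change.* That dose is the area "under the protocol-defined cooling baseline value of 35 °C within 72 h of randomisation", with compliance set at 72 degree-hours. At 34.8 °C a patient gains 0.2 degree-hours per hour; even 1 °C below for an assumed 3 h adds 3, and 3 / 72 is about 4% of the cut-off. Excluding such patients from one arm only could also bias the comparisons built on that dose.
- *That the dose-effect section cannot answer its question at all.* The parallel 34 °C analysis is less affected, and the share at 35 °C may be small.

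**Conclusion.** The point holds as a flaw in a stated rule, not as a missing detail: the article gives both the eligibility table and the category definition, and together they place already-cold patients in the fastest tertile. That they score zero, or the time of their first reading, follows from the wording; the plan does not say it. The possible size runs from 15% of the fastest tertile (5% already cold, all reaching 35 °C) to 86% (20% already cold, 30% never reaching it). All of these figures rest on assumed shares and on about 255 patients in the cooling arm.

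The reach is limited. The intensity comparison is non-randomised, the SAP article calls all secondary outcomes hypothesis-generating, and it bases the trial's conclusions on the primary intention-to-treat analysis, which is untouched.

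**What to change.** In Dose effect / Intensity of cooling, add a rule for each threshold separately: patients whose core temperature closest to, and not after, randomisation is at or below the threshold form their own category, and the tertiles of time are formed only among patients above it at randomisation who later reach it. The category for those never reaching the threshold stays as it is. State the rule for patients with no reading at or before randomisation. Report the number in the new category, which would replace the assumed shares above.

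This concerns only the analysis categories; it asks for no change to eligibility, treatment or the area-under-the-curve dose. The cost is a sentence or two in the plan, minor programming with a temperature already recorded, one more category and slightly smaller tertiles. With all reaching 35 °C, tertile size falls from 85 to (255 − 12.75) / 3 ≈ 81 at 5% already cold, (255 − 25.5) / 3 ≈ 77 at 10%, and (255 − 51) / 3 = 68 at 20%. The article describes six-month outcome collection as still to be completed, so the rule can be set before the analysis.
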